#### Secondary objectives

To investigate the impact of SMART Work & Life, delivered with and without a height adjustable workstation, over the short (assessed at 3 months), medium (assessed at 12 months) and longer term (assessed at 24 months) on;daily sitting time (3 and 12 months)sitting time during working hoursdaily prolonged sitting time and inside/outside of working hoursdaily standing time and inside/outside of working hoursdaily light and moderate-to-vigorous physical activity and inside/outside of working hoursdaily stepping time and number of steps and inside/outside of working hoursadiposity (BMI, percent body fat, waist circumference)blood pressureblood markers (e.g. blood glucose, cholesterol, triglycerides)musculoskeletal issuespsychosocial variables (e.g. fatigue, stress, anxiety and depression, work engagement, job performance and satisfaction, presenteeism, sickness absence, and quality of life)sleep

We will also conduct a full process evaluation and a full economic evaluation.

## Methods

### Design and randomisation

This is a three-arm cluster randomised controlled trial (RCT) aiming to recruit 33 clusters. Clusters will be randomised at the office level to reduce the risk of contamination. Using computer generated lists, office groups (clusters) will be randomised by a statistician from the Leicester Clinical Trials Unit to one of the three groups, stratified by Council area (e.g., Leicester) and cluster size (< 10 participants, ≥10 participants). Randomisation will be performed in batches after clusters have completed their baseline measures. The clusters will be recruited from Councils within the Leicester, Manchester and Liverpool areas in the UK. We aim to recruit 660 office workers across the 33 clusters. Clusters will be randomised to receive one of the following conditions: 1) The multi-component SMART Work & Life intervention with a height-adjustable workstation (intervention 1), or 2) The multi-component SMART Work & Life intervention without a height-adjustable workstation (intervention 2) or 3) usual practice (control condition). Measurements will be repeated, using identical standardised procedures, at 3 months to assess any short-term changes and 12 months and 24-months to assess any longer term changes. Observations, questionnaires and focus groups with office workers and workplace champions will be conducted throughout the intervention period as part of our full process evaluation. This study will be conducted, analysed and reported according to the Consolidation Standards of Reporting Trials (CONSORT) statement for cluster RCTs. Given the nature of the study it is not possible to blind the participants to which intervention they receive. Measurement team members, apart from the team lead, were blinded to group randomisation. Ethical approval has been sought and obtained from the University of Leicester’s College of Life Sciences and University of Salford’s Research, Enterprise and Engagement Ethical Approval Panel. The University of Leicester will act as study sponsor. Figure 1 shows the overall study design.

**Fig. 1 Fig1:**
[figure not shown]
Study design

### Setting

This study is targeting office workers within City and Borough Councils within the Leicester, Manchester and Liverpool areas, UK.

### Cluster and participant recruitment

The study will be advertised in several ways (these have been informed by Councils themselves):Using the councils’ weekly newsletterUsing the councils’ intranetThrough Manager meetingsDisplaying posters on display boardsThrough more targeted strategies directly to appropriate office-based departments e.g., office walk arounds

It will be made clear in the study adverts that the study is looking to recruit office-based employees who spend the majority of their work and waking day sitting down (see inclusion criteria) and that the study will be looking to recruit as many employees within the same office space as possible. Employees who want to hear more about the study will be invited to a presentation where the study will be explained. At the end of the presentation participant information sheets and reply slips (which will include a pre-screening questionnaire to gather basic information to assess eligibility) will be given out to employees who are interested in taking part. The study team’s contact details will also be provided on all study recruitment material so that interested employees can request a participant information sheet directly from the research team.

### Inclusion and exclusion criteria

Participants who meet the following criteria will be eligible:Spend the majority of their day sitting (> 50%). This will initially be self-reported and be used as screening criteria prior to the consent and baseline measurement visit. This will subsequently be confirmed using the objective data collected via the activPAL device (see measures section).Work for the council at least 60% full time equivalent.Work in the same office at least 3 days per week.Be willing and able to give informed consent to take part in the study.Able to walk without the use of an assistive device or requiring assistance from another person.

The participant may not enter the study if any of the following apply:They are currently pregnant.Currently using a height-adjustable workstation at their primary work location.Unable to communicate in English.Unable to provide written informed consent.

### Sample size

The primary analysis will be performed using linear multilevel models, which require a minimum of 10 clusters per arm in order to robustly estimate random effects [29]. Power calculations indicated that with a sample size of 10 clusters per arm and an average cluster size of 14, this study would have over 90% power to detect a 60 min reduction in overall sitting time with a two-tailed significance level of 5%. The calculations assumed a standard deviation of 90 min (informed by SMArT Work, [27]), a conservative intraclass correlation coefficient (ICC) of 0.05 (informed by Stand Up Victoria, [28]), a coefficient of variation to allow for variation in cluster size of 0.54. These calculations allowed for multiple comparisons against the control group. The number of clusters per arm has been inflated by 1 to allow for whole cluster drop out and the sample size was also inflated by 30% to allow for potential individual loss to follow-up and non-compliance with the primary outcome (inflating the n per cluster from 14 to 20). This gives a total sample size of 660 to be recruited, with 11 clusters per arm. Finally, the sensitivity of power was assessed against alternative ICC values of 0.021 and 0.10 [28]. Adequate power for RCTs is widely accepted as 80%, and with these ICC values the power was above the required level at 98 and 81%, respectively.

### Intervention conditions

#### Background

The SMART Work & Life intervention is a multicomponent intervention promoting positive changes in daily sitting and movement in office workers. SMART Work & Life has been developed with input from office workers, local council office workers, workplace champions, council stakeholders, recently published research, experiences in Australia (the Stand Up Australia programme of research e.g., Stand Up Comcare and Stand Up Victoria) [30], and a 12-month RCT of a previous version of the intervention - SMArT Work [24, 27, 31]. As a result, SMArT Work has been refined and extended to become SMART Work & Life. SMART Work & Life incorporates improvements that were noted following the SMArT Work RCT and addresses the gaps in existing interventions by going beyond sitting in the workplace to also focus on behaviour change outside of work, emphasising a novel ‘whole-of-day’ preventive approach to sitting reduction.

SMART Work & Life is grounded in several behaviour change theories (Social Cognitive Theory [32], Organisational Development Theory [33], Habit Theory [34], Self-Regulation Theory [35] and Relapse prevention Theory [36]) and implemented through the Behaviour Change Wheel (BCW) and the associated COM-B approach [37].The latter has ‘capability’, ‘opportunity’, and ‘motivation’ as central components in guiding ‘behaviour’.

#### Intervention goal

The aim of the intervention will be to promote and maintain at least a 60 min per day reduction in daily sitting time compared to usual practice at 24 months. Recent experimental evidence has demonstrated a reduction in glucose, insulin and blood pressure following regular standing and walking breaks (i.e., every 20–30 min), with total reductions in sitting varying from 28 min to 60 min across the course of a day [12, 13, 15, 16, 18]. Furthermore, using statistical modelling we have observed that interchanging 30 mins/day of sitting (measured with the activPAL) with standing and stepping is associated with favourable differences in insulin sensitivity [9] and inflammation [10]. In a similar analysis, interchanging 2 h of sitting/day with standing or stepping was associated with favourable differences in glucose, triglycerides, cholesterol and waist circumference [11]. Others have also shown that each additional hour/day of sitting past 7 h and 8 h is associated with a 5 and 4% higher risk of all-cause mortality in the general population [38, 39]. Thus based on the available evidence, a reduction in sitting time of 60 min per day is likely to represent a clinically meaningful difference in behaviour.

#### Main intervention components

*Organisational strategies* grounded in Social Cognitive Theory and Organisational Development Theory (targeting ‘opportunity’ & ‘motivation’ through BCW intervention functions: enablement, persuasion, environmental restructuring, modelling, positive emotion): 1) we will seek buy-in from the management through the briefing events by explaining the importance of reducing and breaking up sitting at work and how this may lead to workplace benefits without negatively affecting performance and productivity; 2) a brief awareness session (online/video) will reinforce the benefits for the workforce and employers of reducing sitting time in and outside of work and encourage them to brainstorm organisational strategies that could take place, review any current policies around being active at work as well as create new policies around topics such as standing and walking meetings, provision for lunch time walking, internal competitions and displaying signs around the workplace. We will also encourage managers to review the layout of their office space to promote increased movement of staff e.g., location of printers, waste bins, water coolers; 3) Modelling of the positive behaviour from managers will also be emphasised.

*Environmental strategies* grounded in Social Cognitive Theory, Organisational Development Theory and Habit Theory (targeting ‘capability’, ‘motivation’ & ‘opportunity’ through BCW intervention functions: environmental restructuring, enablement as well as ‘automatic’ forms of motivation, including emotion): 1) Small-scale environmental restructuring in the office and at home (e.g., relocation of printers and waste bins), 2) Motivational and reminder signs around the office space and at home to sit less and move more, 3) A height-adjustable workstation to allow the individual to sit or stand to work. The individual will get a choice of desk platform within a set budget. This allows flexibility for office set up, participant preference and avoids testing the effectiveness of a specific type of desk rather than the concept.

*Individual and group strategies* grounded in Social Cognitive Theory, Self-Regulation Theory and Relapse Prevention Theory (targeting ‘capability, ‘motivation’ & ‘opportunity’ through BCW intervention functions: enablement, persuasion, education and training): 1) An initial online education session which covers health consequences of sitting and benefits of reducing and regularly breaking up sitting. The session encourages participants to estimate their own sitting time, brainstorm strategies to reduce sitting at work and outside of work, consider barriers to reducing and breaking up sitting and ways to overcome these barriers. At the end of the session individuals will be encouraged to set a goal around sitting less and an action plan to achieve this. The focus on overall daily sitting will be emphasised rather than just workplace sitting; 2) Self-monitoring of sitting behaviour across the whole waking day will be encouraged through the use of free computer prompts, timers and mobile phone apps. For example, the Rise & Recharge app. The importance of self-monitoring and prompts will be introduced during the education session and the choice of apps, computer software and prompts will be presented during the session; 3) Workplace champions will receive training to encourage their colleagues, deliver brief group coaching, implement competitions and send emails. The coaching sessions will be used to discuss progress, review goals and action plans, discuss personal or social barriers and any benefits experienced. These coaching sessions will take place four times during the intervention period; 4) Workplace champions will send out monthly motivational/education emails; 5) Social support, from colleagues and family members, will be encouraged through regular activity competitions inside and outside of work.

#### Intervention arms 1 and 2

Both intervention arms will receive all of the intervention components listed in the previous sections. However, intervention arm 2 will not receive a height-adjustable workstation. By having both intervention arms receive the same intervention with the exception of the workstation will allow us to investigate how important providing this component is for reducing sitting.

#### Control arm

Office clusters assigned to the usual practice control arm will be asked to continue with their usual occupational health promotion conditions. Participants in the control arm will be asked to complete the same study measurements as those in the intervention arms, at the same time points.

### Measurements

The outcome measurements (unless stated otherwise) will be assessed at four time points; baseline and 3, 12 and 24 months following baseline by a team of researchers who have undergone relevant training. At the baseline visit, the study will be fully explained to the participant again and written informed consent will be obtained if the participant is happy to take part in the study. The consent procedure will be performed by a researcher with appropriate consent training. Only once informed consent has been given will measurements be taken.

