#### Objectively measured sitting and physical activity

The activPAL™ micro device will be worn on the thigh 24 h/day for 7 days. It will be made waterproof using a nitrile sleeve and waterproof medical dressing. This device will assess a variety of aspects of behaviour including sitting, standing and stepping time (total and light and moderate-to-vigorous), prolonged sitting and standing, number of steps and number of transitions from sitting to an upright posture. These variables will be calculated daily (i.e., across all waking hours) and during work hours only. Participants who provide an adequate number of valid days will receive a £10 voucher at the end of each data collection time point. The activPAL is commonly used in sedentary behaviour and physical activity research [40] and has been found to be a valid and reliable measure of sitting, standing, stepping and postural transitions in adults [41–43]. The activPAL data will be cleaned and processed using a previously published automated algorithm [44].

A wrist-worn accelerometer will also be worn on the non-dominant wrist 24 h/day for 7 days. Time spent in different intensities of physical activity as well as sleep duration and other sleep variables such as efficiency will be calculated.

Participants will be asked to complete a short log each day to note the time they went to bed, went to sleep, woke up and got out of bed each day, work times, as well as recording any periods throughout the day if they removed the devices.

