#### Work-related measures

Job performance [50] and job satisfaction [51] will be measured using single-item 7-point likert scales. Work engagement (characterized by vigour, dedication, and absorption) will be measured using the Utrecht Work Engagement Scale [52]; a multi-item 7-point likert scale. The Need for Recovery Scale [53] will be used to measure occupational fatigue. Musculoskeletal symptoms will be assessed using the Standardised Nordic Questionnaire [54]. Work load and relations will be assessed using the demands, control and support scales from the Health and Safety Executive Management Standards Indicator Tool using a 5-point likert scale [55]. Sickness presenteeism will be assessed by the validated 8-item Work Limitations Questionnaire [56] which asks participants to rate on a six-point Likert scale how their health has affected aspects of their work in the past 2 weeks. Data on sickness absence will be collected using both self-report and from employer records and include frequency and duration of self-certified and certified sickness. Reasons for sickness absence will also be recorded. Data on sickness absence will be collected for 12 months prior to the intervention and for the 24 months of the intervention period.

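### Visits are timed from baseline but offices are randomised afterwards, in batches, so the 3-month estimate rests on less than 3 months of exposure

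*Protocol article*

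**What the plan says.** Under Measurements, the Protocol article starts the follow-up clock at baseline: outcomes "will be assessed at four time points; baseline and 3, 12 and 24 months following baseline". The sentence opens with an exemption for measures whose timing is given elsewhere ("The outcome measurements (unless stated otherwise").

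Under Design and randomisation, allocation comes later: "Randomisation will be performed in batches after clusters have completed their baseline measures".

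Baseline itself takes time. Under Objectively measured sitting and physical activity: "The activPAL™ micro device will be worn on the thigh 24 h/day for 7 days". The same device checks the sitting criterion for eligibility: "This will subsequently be confirmed using the objective data collected via the activPAL device" (Inclusion and exclusion criteria).

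The Secondary objectives ask for the effect "over the short (assessed at 3 months), medium (assessed at 12 months) and longer term (assessed at 24 months". The Statistical analysis section adds an analysis of the primary outcome that takes all time points together as repeated measures.

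Sickness absence has its own window under Work-related measures: "Data on sickness absence will be collected for 12 months prior to the intervention and for the 24 months of the intervention period".

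Control participants are measured on the same schedule as the intervention arms (Control arm).

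**The concern.** The visit clock starts before anyone knows which arm an office is in. Time spent finishing baseline, waiting for the batch to be randomised and setting up the programme is therefore counted as follow-up. A visit labelled 3 months sees less than 3 months of intervention. Because randomisation is batched, the shortfall need not be the same in every office.

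Two results are exposed. The first is the short-term effect at 3 months, a stated secondary objective, which is diluted to the extent that the effect depends on time under intervention. The second is the profile over 3, 12 and 24 months: a rise from 3 to 12 months could reflect a late start as well as a gradual build-up, and the planned analysis could not tell these apart.

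Sickness absence raises a related question. Its window is defined by the start of the intervention, an event that does not occur in a usual-practice office. Absence is a secondary outcome and also enters the economic evaluation, so its window needs a start date that exists in all three arms.

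**Working it through.** **Order of events.** Visits count from baseline (Measurements). Randomisation follows completed baseline measures (Design and randomisation). Desk, champion training and education belong to the intervention arms only (Main intervention components; Intervention arms 1 and 2), so they cannot be given to an office as its intervention before it is allocated. Hence baseline precedes randomisation, which precedes intervention start, and exposure at every visit is less than the visit's nominal time. This follows from the stated rules and needs no assumed figure.

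**The plan's own figures.** The inputs under Sample size are 10 clusters per arm, mean size 14, difference 60 min, SD 90 min, ICC 0.05 and coefficient of variation of cluster size 0.54. I take 2.5% two-sided per comparison as the allowance for two comparisons with control; that split is my assumption.

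- Design effect = 1 + ((1 + 0.54²) × 14 − 1) × 0.05 = 1.854.
- Effective n per arm = 140 / 1.854 = 75.5.
- Power from a non-central t with 18 degrees of freedom (10 + 10 − 2) = 94.1%, against over 90% stated.
- At ICC 0.021 and 0.10 the same method gives 98.6% and 81.8%, against 98% and 81% stated.
- 14 / 0.70 = 20 per cluster, and 3 × 11 × 20 = 660, as stated.

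The figures reproduce. No timing input enters the calculation, so changing the visit anchor leaves sample size and power as they are.

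**Exposure at each visit.** Let L be the gap in months from baseline to intervention start. The article does not give L, so the values below are assumptions. Exposure at visit month v is v − L, and as a share of nominal it is (v − L) / v.

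| Assumed L | 3 months | 12 months | 24 months |
|---|---|---|---|
| 0.5 | 2.5 / 3 = 83% | 11.5 / 12 = 96% | 23.5 / 24 = 98% |
| 1 | 2 / 3 = 67% | 11 / 12 = 92% | 23 / 24 = 96% |
| 2 | 1 / 3 = 33% | 10 / 12 = 83% | 22 / 24 = 92% |

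These are shares of time under intervention, not of effect. How much of the effect is lost depends on how quickly behaviour changes, which the article does not specify.

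**The absence window.** In an intervention office, the 12 months before and 24 months after can be counted from the start of the programme. In a control office the Control arm section only asks for usual practice to continue, so there is no such date to count from.

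**The case against.** The strongest reply is that the schedule is the same for all arms and the analysis is by allocated group, whatever was received. Waiting for a batch happens before allocation and is balanced in expectation. Set-up time is part of what an employer adopting the programme would experience, so including it is a legitimate policy-type estimate. This stands. A reader might infer that the comparison with control is biased, but nothing in the article supports that.

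The size is also assumed. The article gives no lag, does not say how batches are formed, and does not say whether baseline means the first visit or the completion of baseline measures. In the latter case the 7 days of device wear are not lost exposure. This stands too: the article shows that exposure is shorter than nominal and may vary, not by how much.

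A reader might infer that the desk arm is disadvantaged at 3 months, because there "The individual will get a choice of desk platform within a set budget" and desks must then be supplied. The article does not say that desks arrive later than the education or champion training, so an extra delay in that arm is possible but not shown.

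A reader might also see a contradiction between visits 24 months after baseline and a 24-month intervention period. That fails. The latter phrase sets the window for absence data, and Measurements allows other timing where it is stated. Only the missing start date for control offices remains.

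Finally, visit windows and date logging are usually left to the full protocol. That is fair, but the point here is a stated anchor, not an omitted detail.

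**Conclusion.** The point holds as a minor one. Exposure at the 3-month visit is necessarily under 3 months and can differ between batches. Under an assumed gap of 0.5 to 2 months it is 83% to 33% of nominal, against 96% to 83% at 12 months and 98% to 92% at 24 months. The loss therefore falls mainly on the secondary 3-month estimate and on the reading of the time profile in the repeated-measures analysis. The randomised comparison is not biased, the primary 24-month result is little affected, and the sample size and power do not change. The absence window is a separate clock that the article permits, but it lacks a defined start in control offices. The ordering of events follows from the text; every percentage rests on the assumed gap.

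**What to change.** Time the 3-, 12- and 24-month visits from one common date per randomisation batch, applied equally to all three arms. A launch date fixed at randomisation is preferable, because it can also take set-up time out of the follow-up interval. The randomisation date would remove only the wait up to allocation. Use the same date for the 12-month look-back and the 24-month collection of sickness absence, so that control offices have a defined window. Record, by office, the dates of baseline, randomisation, first education session and desk installation, so that actual exposure at each visit can be reported and any desk delay seen.

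The cost is a wording change and a shift of some weeks in the visit calendar, with no extra visits. The downside is that visits move off the calendar month of baseline and the interval since baseline varies slightly between offices, equally across arms.
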